##### Inclusion criteria

Any manufacturing multinational workplace that employs more than 250 employees and has a daily workplace canteen for employees can be included in the study. The workplace must be located in Cork, represented on the Industrial Development Agency (IDA) website and able to commit to all components of the complex intervention for the duration of the study.

Any permanent, full-time employee who is contracted to work for the duration of the study period and purchases and consumes at least one meal in the main canteen daily will be eligible to participate in the study.

##### Exclusion criteria

All non-manufacturing national workplaces that employ less than 250 employees or do not have a workplace canteen; are not represented in the IDA website; not located in Cork or not able to commit to the intervention design for the study period will be excluded.

Employees will be excluded if they:

1. Work part time.

2. Do not have contracts to work during the study period.

3. Do not work in the workplace full-time (for example, work from home 2 days a week).

4. Travel regularly for work (more than once a month).

5. Do not purchase and consume a main meal from the staff canteen daily.

6. Are medically advised not to participate in the study.

7. Are involved in an on-going diet programme external to work (for example, the Weight Watchers programme).

##### Data collection methods

All data collection will take place during paid working hours (excluding employees’ breaks). To measure the effects on the primary and secondary outcomes, data will be collected in four stages using questionnaires, dietary and physical assessments and face-to-face semistructured interviews. Baseline assessments will be conducted prior to implementation of the intervention. Follow-up assessments will be carried out at 3 to 4 months, 7 to 9 months and 13 to 16 months.

##### Questionnaires

Four questionnaires will be self-completed by each participant electronically or in a hard-copy format. All questionnaires are based on validated, pre-tested questionnaires and will be completed at various study time-points.

The Health, Lifestyle and Food Questionnaire (HLFQ) is organized into ten different sections (A to J). Sections A, B, and C relate to the participant (sex, age, ethnicity, education), and include details of work life (permanent or temporary, job arrangement) and general health status (self-rated health, health conditions and self-rated weight) [27] Sections D, E and F relate to the participant’s usual dietary patterns at home and at work. Sections G, H and I investigate the participant’s usual lifestyle patterns including physical activity (using the International Physical Activity Questionnaire), smoking and alcohol questions [28]). Section J will focus on the participant’s nutrition knowledge using the General Nutrition Knowledge Questionnaire (GNKQ) [23]. The questionnaire will take approximately 25 minutes to complete.

The Food Motives Questionnaire (FMQ) will investigate motives underlying the selection of food [20]. It consists of nine scales, including health, mood, convenience, sensory appeal, natural content, price, weight control, familiarity and ethical concern. This questionnaire will help understand the causes of variation in dietary intake among participants. This questionnaire will take five minutes to complete.

The Dutch Eating Behaviour Questionnaire (DEBQ) is a validated eating behaviour scale to assess restrained, emotional and external eating behaviour [21]. The questionnaire will take three minutes to complete.

The EuroQol-5D (EQ-5D) is a standardized instrument for use as a measure of health outcome. Applicable to a wide range of health conditions and treatments, the EQ-5D health questionnaire provides a simple descriptive profile and a single index value for health status [29]. EQ-5D is primarily designed for self-completion by participants and is ideally suited for use in online surveys and face-to-face interviews.

##### Dietary assessments

The 24-hour dietary recall method will quantitatively measure current nutrient intake over a period of 24 hours, including the workplace and the home environment. Little burden is placed on the participant as this method requires short-term memory only but it fails to measure habitual diet. The Food Frequency Questionnaire tool is used to measure habitual dietary intake. It is a quantitative instrument and the most commonly used dietary assessment in large scale epidemiologic surveys.

The Food Frequency Questionnaire (FFQ) will be self-completed by each participant electronically or in a hard-copy format at baseline and follow-up at 7 to 9 months and 13 to 16 months. The FFQ is an adapted version of the European Prospective Investigation of Cancer FFQ [30]. It has been used extensively in the Irish population including the Irish Surveys of Lifestyle, Attitudes and Nutrition [28] and the original Cork and Kerry baseline study in 1998 [31] and the baseline Phase II Cork and Kerry study in 2010 [32]. The FFQ is designed to assess the whole diet and includes 150 food items arranged into the main food groups. Respondents will be asked to record their average frequency of consumption of each food item over the last year. Typical weights, portion sizes and nutrient intake will be based on recommendations established by the Food Standards Agency (2002) [33] and McCance and Widdowson’s Food Composition Tables [34,35]. A specifically designed programme, NetWISP4© (Weighed Intake Software Program; Tinuviel Software, Warrington, UK), will convert dietary information to food quantities and nutrient values [36,37].

The 24-hour dietary recall method will be a modified version of the validated UK 24 hour dietary recall method [38]. Two dietary recalls will be collected within one week to examine on- and off-work-duty dietary patterns at baseline, and follow-up periods of 3 to 4 months, 7 to 9 months and 13 to 16 months.

The three-step method will outline specifically what the participant had to eat and drink in the previous 24 hour period.

1. Quick list: participants will be asked to report everything that they had to eat or drink the day before their appointment (midnight to midnight).

2. The nutritionist or research assistant will collect detailed information on items named in the quick list (consumption time, place of consumption, brand and recipe), foods likely to be eaten in combination (milk in coffee) and the quantity consumed and any leftovers or second helpings.

3. Recall review: participants will have an opportunity to provide additional information or to refer to foods forgotten in the quick list.

Finally, the interviewer will ask the participants about their consumption of water and food supplements. All information gathered is recorded in a food consumption record. Additional modifications added to the method include specific prompts to measure salt and oil consumption. Each 24-hour dietary recall data collection will take approximately 20 minutes to complete. Finally, the nutritionist or research assistant will complete an interviewer evaluation. Each food, drink and portion size will be coded according to the 24-hour coding instructions based on the validated UK method. Food and nutrient analysis will be calculated using NetWISP4© (Weighed Intake Software Program; Tinuviel Software, Warrington, UK) [36,37].

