**Figure 2 F2:**
[figure not shown]
Food Choice at Work trial design.

Study outcomes will assess the effect of the intervention on dietary behaviours and improvements in diet-related disease risk. Primary outcomes will include changes in dietary behaviour and health status. Analysis of multiple 24-hour dietary recalls, food frequency questionnaires, food sales data and food purchasing patterns will indicate changes in dietary behaviour. Changes in body mass index (BMI), waist circumference, resting blood pressure and urinary electrolytes, including sodium and potassium (24-hr urine collections and random urine samples) will highlight improved health status outcomes. Secondary outcomes will determine food motives [20] and eating behaviours [21], changes in nutrition knowledge [22] and economic cost outcomes. A cost-effectiveness economic evaluation will be conducted and absenteeism trends will be recorded during the study period.

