##### Study duration

The total study duration is 16 months, with the interventions being delivered over a 9-month period. Follow-up is for 6 months post-intervention.

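### The FFQ asks about the last year but the intervention lasts nine months, so the FFQ understates effects at 7-9 months and can make a faded effect look sustained at 13-16 months

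*Protocol article*

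**What the plan says.** Under Modelling process and outcomes (the text after Figure 2), the article states: "Primary outcomes will include changes in dietary behaviour and health status". It names four sources for the dietary part: "Analysis of multiple 24-hour dietary recalls, food frequency questionnaires, food sales data and food purchasing patterns will indicate changes in dietary behaviour".

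Under Dietary assessments, the FFQ is scheduled "at baseline and follow-up at 7 to 9 months and 13 to 16 months", so none is taken at 3-4 months. Its reference period is fixed in one sentence: "Respondents will be asked to record their average frequency of consumption of each food item over the last year". No different period is given for follow-up. The same section assigns habitual intake to the FFQ and concedes that the 24-hour recall does not capture it. Two recalls are taken at each of the four stages.

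On timing, Study duration describes the trial "with the interventions being delivered over a 9-month period" and adds: "Follow-up is for 6 months post-intervention". Data collection methods states: "Baseline assessments will be conducted prior to implementation of the intervention". Long-term follow-up gives the reason for the last visit: to see whether dietary changes are sustained.

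**The concern.** A 12-month recall window cannot fit inside a 9-month intervention, nor inside a post-intervention period of about six months. Each follow-up FFQ therefore averages over two phases that the trial wants to tell apart.

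The two visits are affected differently. At 7-9 months the window reaches back before the intervention began, which pulls the FFQ contrast toward no effect. At 13-16 months the window holds no pre-intervention time. It mixes delivery months with post-delivery months, so a diet that has reverted still carries credit for the delivery period.

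At stake are the FFQ reading of the end-of-intervention effect and the FFQ reading of sustainability, which is the stated purpose of the last visit. The article's Limitations section discusses recall and social desirability bias in the FFQ but does not mention this overlap.

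**Working it through.** **Inputs.** Recall window 12 months and FFQ visits at 7-9 and 13-16 months (Dietary assessments); delivery 9 months (Study duration). Assumption: visit months are counted from the start of the intervention. The article gives no figure for the overlap, so there is none to reproduce.

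**Step 1: split the window.** For a visit at month t:

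- pre-intervention months = max(0, 12 − t)
- delivery months = min(t, 9) − max(t − 12, 0)
- post-delivery months = max(0, t − 9)

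| Visit month | Pre | Delivery | Post | Share outside the phase of interest |
|---|---|---|---|---|
| 7 | 5 | 7 | 0 | 5/12 = 42% pre |
| 8 | 4 | 8 | 0 | 4/12 = 33% pre |
| 9 | 3 | 9 | 0 | 3/12 = 25% pre |
| 13 | 0 | 8 | 4 | 8/12 = 67% delivery |
| 14 | 0 | 7 | 5 | 7/12 = 58% delivery |
| 15 | 0 | 6 | 6 | 6/12 = 50% delivery |
| 16 | 0 | 5 | 7 | 5/12 = 42% delivery |

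**Step 2: translate into effect size.** Assume that respondents weight the 12 months equally, that the effect is immediate and constant during delivery, and that a fraction r of it remains afterwards. The FFQ then shows (delivery + r × post)/12 of the delivery effect.

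- Months 7, 8 and 9: 7/12 = 58%, 8/12 = 67%, 9/12 = 75%.
- Months 13 and 16, effect wholly lost (r = 0): 67% and 42%.
- Months 13 and 16, effect halved (r = 0.5): (8 + 2)/12 = 83% and (5 + 3.5)/12 = 71%.
- Months 13 and 16, effect fully kept (r = 1): 100% and 100%.

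**Step 3: compare the two FFQ visits.** If the effect vanished at month 9, someone seen at months 7 and 13 would go from 58% to 67%, at months 8 and 14 from 67% to 58%, and at months 9 and 15 from 75% to 50%. A lost effect can thus look stable or even growing on the FFQ. A fully kept effect would appear to rise from 58-75% to 100%.

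**Step 4: illustrate the cost in power.** Determination of sample size gives a 2 g salt difference, SD 4.2 and 112 per workplace. Take one workplace against another at two-sided 5%, ignore clustering, and suppose that salt were read from the FFQ (the article does not say which instrument supplies it). Per-arm n for 80% power = 2 × (1.960 + 0.842)² × 4.2² / d².

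- Undiluted, d = 2 g: n = 70, and power with 112 per arm is 95%. This agrees with the article's statement of adequate power for salt, before clustering.
- Month 9, d = 2 × 0.75 = 1.50 g: n = 124, power 76%.
- Month 7, d = 2 × 0.583 = 1.17 g: n = 204, power 55%.

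These figures show scale only. They do not recalculate the trial's power.

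**The case against.** The strongest reply is that the FFQ is one of four dietary sources, and the others have no one-year window. The recalls are taken at every stage. Urinary sodium is measured at baseline, 7-9 and 13-16 months. The salt validation study tests the recalls, with the FFQ only a comparator. The Statistical analysis section does not tie the intake analysis to the FFQ. All of this stands, and it confines the point to the FFQ component.

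The percentages are also modelled. Respondents may give recent months more weight, which would shrink both distortions by an unknown amount; an effect that builds up slowly would change the figures too. This qualifies the size. It does not alter the calendar or the period that the question asks about.

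A third reply is that a one-year frame belongs to an established instrument and averages out season. That is a real advantage, and it counts against simply shortening the window at follow-up. Change from baseline would then compare two different reference periods. With one workplace per arm and visit windows several months wide, season could also be confounded with workplace.

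A reader might infer that the last FFQ cannot address sustainability at all. The model above does not support that: at 13-16 months full persistence gives 100% and complete loss gives 42% to 67%, and these do not overlap. The FFQ blurs the question, and the recalls at that visit address it directly.

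**Conclusion.** The point holds for the FFQ component of the primary dietary outcome. The month counts follow from the article's own text, and nothing in it offsets them. At 7-9 months the FFQ is biased toward the null, showing 58% to 75% of a full effect under equal month weighting and an immediate, constant effect. At 13-16 months 67% to 42% of the window is delivery time, so persistence is overstated if the effect fades.

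The counts assume that months run from the start of the intervention. If they run from an earlier baseline visit, the pre-intervention share at 7-9 months is larger.

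Three stronger readings are tempting but unsupported:

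- That the primary outcome as a whole is diluted. The recalls, sales data, BMI, blood pressure and urine measures are untouched.
- That both follow-up visits suffer dilution. At 13-16 months a fully sustained effect would be shown in full; the fault there is mixing.
- That the FFQ is the only instrument concerned with usual diet. Sections D to F of the Health, Lifestyle and Food Questionnaire also ask about usual dietary patterns.

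The plan should be changed, but the flaw does not undermine the other outcomes.

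**What to change.** **Preferred.** State that the end-of-intervention (7-9 month) and post-intervention (13-16 month) dietary contrasts rest on the 24-hour recalls already scheduled at all four stages. Keep the sales and purchasing data in their present role. Report the FFQ as supportive, with the window overlap at each visit stated beside its results. This needs no new data and takes the bias out of the main dietary conclusion. The cost is that two recalls per stage represent habitual diet less well, as the article acknowledges.

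**If the FFQ is to stay a main measure of change.** Use a shorter reference period that fits inside each phase, for example the last 3 months. That lies wholly within delivery at months 7-9 and wholly after it at months 13-16. Use the same period at baseline and follow-up where baseline has not yet been collected (Trial status reports recruitment as still open), make it identical in all four workplaces, and check that the workplaces are assessed in the same season. The costs are departure from the established instrument and more seasonal variation. Where baseline has already been taken on the one-year frame, the preferred option avoids mismatched periods.

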##### Physical assessments

Each participant will be asked to participate in a physical assessment where BMI, (midway) waist circumference, waist hip ratio and resting blood pressure will be measured.

##### Resting blood pressure

Blood pressure measurements will be obtained using the Omron M7 Digital Blood Pressure monitor. It is a compact, fully automatic monitor, operating on the oscillometric principle. This method of measurement determines the participant’s blood pressure by measuring the pressure fluctuations caused by the pulse waves. Before the measurement begins, the participant will be seated and as relaxed as possible with both feet parallel and flat on the floor. The researcher will ensure that the participant has not been smoking or participating in any vigorous exercise prior to the measurement. A full bladder also affects a blood pressure reading, so the researcher will give the participant an opportunity to void prior to measurement.

The researcher will instruct the participant to remove any tight clothing covering the upper arms and ensure that the participant has been seated and settled for approximately 5 minutes prior to commencing the procedure. The measurements will be taken on the right arm whenever possible. The participant’s arm will rest on a desk so that the antecubital fossa (a triangular cavity of the elbow joint that contains a tendon of the biceps, the median nerve and the brachial artery) is at the level of the heart and the palm is facing up. The participant must always feel comfortable. The greatest circumference of the upper arm will be measured for a suitable cuff, with the arm relaxed and in the normal blood pressure measurement position (antecubital fossa at the level of the heart), using an inelastic tape. Three measurements will be taken from each participant one minute apart.

##### Urine analysis

Spot urine samples will be obtained for analyses of sodium, potassium, urea and creatinine levels. Two spot urine samples will be obtained from each individual at baseline and follow-up periods of 7 to 9 and 13 to 16 months (six spot samples in total per participant). Each participant will provide one sample from the evening before their on-duty 24-hour dietary recall and their second sample will be the first sample voided on the morning of their dietary recall. The urine samples will be taken approximately 12 hours apart, for example, 8 pm and 8 am.

A subsample of participants from each workplace will be asked to complete a 24-hour urine collection the day before their on-duty 24-hour dietary recall at baseline and at follow-up periods of 7 to 9 and 13 to 16 months. 24-hour urinary sodium excretion is considered the gold standard method for estimating dietary salt intake. It is estimated that between 90% and 95% of dietary salt intake is excreted in urine. Para-aminobenzoic acid, a biologically inert substance that is rapidly excreted in urine, will be administered to all participants on the day of urine collection to validate the completeness of the 24-hour collection sample. To estimate total sodium excretion in the spot urine samples, the sodium content will corrected for total 24-hour urine volumes calculated from the validated 24-hour urine samples collected.

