No sauces or accompaniments will be added to any meal unless the employee requests it. Chips and French fries will be removed from the menus two days a week and replaced with different potato options, for example baked potatoes. Pizzas will be removed from the menus three days a week. All desserts will be fruit-based. Soft carbonated drinks will be restricted and replaced with water, milk and unsweetened fruit juice options.

To increase fibre, fruit and vegetables, white pasta, rice and bread will be replaced with wholegrain alternatives. Fruit and vegetables will be added to rice, pasta, soup and meat dishes. A buffet-style fresh salad bar will be available to accompany any dish daily. Fresh whole fruit will be available throughout the day.

Portions of whole fruit will be offered at discount prices.

To introduce portion size control, workplaces will be recommended to comply with the FSAI guidance on portion size [23]. Training will be provided to all catering staff regarding strict portion size control. Standard serving tools will be used by caterers and employees to control portion size at mealtimes.

Healthier alternatives will be strategically positioned: healthy snacks, such as whole fresh fruit, dried fruit, nuts without chocolate, salt or sugar, brown sandwiches, brown soda bread and seeds will be positioned at eye level at the entrance of the canteen and in the vending machines. Chocolate, sweets, biscuits and crisps will be restricted and replaced where possible with healthy snacks in the canteen and in the vending machines located in the canteen. Full-size chocolate bars will be replaced with smaller options. Salt will be removed from the tables and will be replaced with sachets.

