#### Testing procedures

In 2009, we carried out a cross-sectional comparison pilot study in two public hospitals in Cork, Ireland; one of which had implemented a long-term (2 years) catering intervention designed to reduce dietary fat, saturated fat, sugar and salt intake. All menus were modified. High-salt products (gravy mixes, stock cubes) and processed meat (bacon, corned beef) were replaced with low-salt options (turkey, chicken and fish). Fresh herbs, spices and garlic were introduced. Salt was removed in cooking. Saltcellars were removed from the tables in the canteen but small salt sachets were available at the service counter. Nutrition information was displayed in the canteen area. No sauces were added to any meals without the employee’s consent. All desserts were fruit-based. Staff members were encouraged to consume extra salad and vegetable options at no extra cost. Cooking methods with oil were reduced. No catering changes were implemented in the second hospital.

A total sample of 100 random employees aged 18 to 64 years (50 from each hospital) who consumed at least one main meal in the hospital staff canteen daily took part in the study. Dietary intakes and sociodemographic characteristics were assessed. Reported mean intakes of total sugars, total fat, saturated fat and salt were significantly lower in the intervention hospital when adjusting for age and sex. Estimated average salt intake in the intervention hospital (5.6 g/day) did not exceed the tolerable upper limit of 6 g/day vs. a mean salt intake of 6.7 g/day in the non-intervention hospital.

The study findings, published in the journal Public Health Nutrition [24], suggest that a structured catering initiative sustained over a relatively long period may influence long-term positive food choices at work and at home. Although these findings should be interpreted cautiously given the small sample size, many of the proposed dietary environmental modification and nutrition education components of the 'Food Choice at Work’ study have been shown to be acceptable and feasible in a workplace setting.

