#### Determination of sample size

A decrease in BMI by 1 kg/m^2^ (1 unit) and a 2 g average fall in dietary salt intake would have population health significance and clinical significance in terms of the risk of diet-related disease, for example, hypertension. To detect this difference in BMI between the control and intervention groups at follow-up session after 7 to 9 and 13 to 16 months and assuming a common standard deviation of 3.77, it is estimated that a sample size of 448 (112 per workplace) would have 80% power at the 5% significance level (findings from a previous study show that a 1 kg/m^2^ difference was independently associated with 13% higher risk for hypertension) [25,26]. The study will also be adequately powered (80% power at the 5% significance level) to detect a fall in dietary salt intake between the control and intervention groups at follow-up periods of 7 to 9 and 13 to 16 months using a standard deviation of 4.2 (In a previous intervention study the response within each participant group was normally distributed with standard deviation 4.2) [27].

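### Spot-urine sodium is converted with 24-hour volumes that exist only for a subsample, and the stated correction omits creatinine, so individual dilution stays in the estimate

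*Protocol article*

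**What the plan says.** The Urine analysis section of the protocol article sets out three things.

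- Everyone gives spot samples: "Two spot urine samples will be obtained from each individual at baseline and follow-up periods of 7 to 9 and 13 to 16 months". The assay panel includes a dilution marker: "Spot urine samples will be obtained for analyses of sodium, potassium, urea and creatinine levels".
- Full collections are restricted: "A subsample of participants from each workplace will be asked to complete a 24-hour urine collection", at the same three time points. Completeness is checked with para-aminobenzoic acid (PABA). The size of the subsample is not given.
- The conversion from spot sample to total excretion is stated in one sentence: "the sodium content will corrected for total 24-hour urine volumes calculated from the validated 24-hour urine samples collected".

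The sentence does not say which volume applies to a participant without a collection, or whether it is specific to workplace and visit. Creatinine does not appear in it.

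The outcomes paragraph after Figure 2 places these measurements, spot samples included, under the primary outcomes: "urinary electrolytes, including sodium and potassium (24-hr urine collections and random urine samples) will highlight improved health status outcomes".

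**The concern.** A spot sample gives a concentration, which depends on sodium excreted and on how dilute the urine is. Multiplying it by the person's own 24-hour volume largely removes the dilution. Multiplying it by someone else's volume, or an average, does not: a person who drinks a lot reads as low in salt and a person who drinks little reads as high. Most of the data may be affected, because only the subsample has its own volumes.

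Urinary sodium is one of the few objective measures here. The Recall bias section relies on objective outcomes because participants cannot be blinded. Noise or bias in the spot-derived values weakens that check.

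The planned validation study also compares recalls with spot samples. If subsample members' spot values are scaled by their own 24-hour volume, the spot estimate and the 24-hour reference share that volume. Good agreement there would not carry over to participants who lack one.

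**Working it through.** The article gives no figure for this conversion, so there is nothing to reproduce. The check is of the measurement algebra.

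**Inputs from the article.** Pilot salt intake, used only to put percentages into grams: "a mean salt intake of 6.7 g/day in the non-intervention hospital", against 5.6 g/day in the intervention hospital. Effect regarded as important: "a 2 g average fall in dietary salt intake would have population health significance". Both concern dietary salt.

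**Assumed inputs.** Between-person CV of 24-hour volume 0.3 to 0.5; CV of sodium excretion 0.4; sodium-volume correlation ρ from 0 to 0.5; both log-normal; CV of 24-hour creatinine about 0.15. Spot concentration is taken as the 24-hour average, so time-of-day variation is set aside.

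**Step 1: what each method estimates.** Let Na, Cr and V be a person's 24-hour sodium, creatinine and volume.

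- Volume scaling: (Na/V) × Vref = Na × (Vref/V). The person's own V remains.
- Creatinine ratio: (Na/V) ÷ (Cr/V) × Cr24 = Na × (Cr24/Cr), where Cr24 is the predicted 24-hour creatinine. V cancels.

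**Step 2: bias in the level.** With Vref the mean volume, and a and b the log-scale SDs of Na and V, the ratio of the estimated to the true mean is exp(b² − ρab). For CV 0.4, a = √ln(1.16) = 0.385. For volume CV 0.3, b = √ln(1.09) = 0.294.

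| Volume CV | ρ = 0 | ρ = 0.3 | ρ = 0.5 |
|---|---|---|---|
| 0.3 | 1.09 | 1.05 | 1.03 |
| 0.4 | 1.16 | 1.11 | 1.08 |
| 0.5 | 1.25 | 1.18 | 1.14 |

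The overstatement is 3% to 25%. It vanishes when b = ρa; at volume CV 0.3 that is ρ = 0.294/0.385 = 0.76, outside the assumed range. A simulation of 400,000 draws (both CVs 0.4, ρ = 0) gave a true mean of 6.69 and a volume-scaled mean of 7.76, a ratio of 1.16.

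**Step 3: error for the individual.** With both CVs 0.4 and ρ = 0:

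- CV of the volume-scaled estimate = √(1.16² − 1) = 0.59, against a true 0.40. At 6.7 g/day the SD rises from 6.7 × 0.4 = 2.7 to 6.7 × 1.16 × 0.588 = 4.6.
- Correlation with true excretion = 0.4/0.588 = 0.68. The creatinine ratio gave 0.93 in the simulation.

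**Step 4: when a false change appears.** Suppose true sodium is constant and volume changes by a fraction f.

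- Vref fixed over time: apparent sodium is multiplied by 1/(1+f). For f = 10%, 1/1.1 = 0.909, a 9% fall, or 0.6 g at 6.7 g/day. For f = 20%, 1/1.2 = 0.833, a 17% fall, or 1.1 g. Matching the pilot difference needs 6.7/5.6 − 1 = 20%; matching a 2 g fall needs 6.7/4.7 − 1 = 43%.
- Vref re-estimated by workplace and visit: (Na/1.2V) × 1.2Vref equals (Na/V) × Vref, so a uniform shift cancels from the group mean. In the simulation the mean was 7.76 before and after. The errors of steps 2 and 3 remain.
- Creatinine ratio: no change, 6.84 before and after. That is about 2% above the true 6.69, from creatinine variation; calibration can absorb it.

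**The case against.** The strongest reply is that the sentence condenses a procedure detailed elsewhere, and that the article mentions a standard operating procedures manual that is not shown. The article does not say that a mean or fixed volume will be used. This stands in part: which volume goes to whom is open. But the article does commit to volume as the basis of correction, and no choice of volume from the subsample gives the remaining participants their own.

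Three stronger readings are tempting and are not supported.

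- **That the plan would create a false intervention effect.** Collections recur in every workplace at each urine visit, so volumes specific to workplace and visit are obtainable and would cancel a uniform shift. The text neither promises nor excludes their use. A constant proportional overstatement shared by all workplaces creates no effect where there is none, although it rescales a real one.
- **That the interventions will raise urine volume.** In workplaces C and D, "Soft carbonated drinks will be restricted and replaced with water, milk and unsweetened fruit juice options". That is substitution, and the documents contain no volume data.
- **That creatinine is ignored altogether.** It is absent from the stated correction; another use is not ruled out.

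Two more points stand. The 2 g figure concerns dietary salt, not spot-derived excretion, so it is only a yardstick here. And measured 24-hour excretion in the subsample, which the article itself treats as the reference method, is unaffected.

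**Conclusion.** The point holds in a limited form. The stated conversion leaves individual dilution in the sodium estimate of every participant outside the subsample, although a marker that removes it is assayed in every spot sample. That follows from the text and the algebra.

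Its size rests on assumed variation. The level is probably overstated, by about 3% to 25% over the assumed ranges, and the bias could be nil at a higher sodium-volume correlation. The between-person CV rises from 0.40 to 0.59 when both CVs are 0.4 and uncorrelated. A false difference in change between workplaces is possible but conditional, as step 4 shows. It should be corrected, with medium confidence in how much it matters, because spot-urine electrolytes sit among the primary outcomes.

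**What to change.** Replace the conversion sentence with a rule on these lines:

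- Estimate 24-hour sodium from the spot sodium-to-creatinine ratio, with 24-hour creatinine predicted from age, sex and baseline weight. Use baseline weight at every visit: weight is itself a target of the interventions, and follow-up weight could carry an intervention effect into the sodium estimate.
- Calibrate one equation in the subsample with PABA-complete collections, and apply it identically to all workplaces and visits.
- Report measured 24-hour excretion in the subsample as the reference result, and check that calibration error does not differ by workplace or visit.

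If volume scaling is kept, the minimum is to state which volume applies to participants without a collection, make it specific to workplace and visit, and add a creatinine-based sensitivity analysis.

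The cost is mainly analysis wording. Spot creatinine, age and sex are already collected, and weight is needed for BMI. The article does not say whether creatinine is assayed in the 24-hour collections; if it is not, the equation can be calibrated directly against measured 24-hour sodium. Calibration uncertainty must be carried into the intervals, and its size depends on the unstated subsample size. Time-of-day variation in sodium remains under either method.
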